#### Secondary endpoints

Incidence of composite cardiovascular events at 3 years after study examinationsCost-effectiveness analysisManagement status (prescription rates of secondary prevention drugs for CAD and rates of achieving management goals for blood pressure, lipids, and diabetes), additional imaging tests (stress myocardial SPECT or 13 N-ammonia positron emission tomography [NH_3_-PET]), and PCI or CABG after study examinationsRate of complications associated with coronary artery HIPs with a plaque-to-myocardium signal intensity ratio (PMR) of ≥ 1.1 or coronary artery HIPs with PMR ≥ 1.4 in patients at very high risk (Suita score of ≥66) and undergoing primary prevention for CADComplication rate for coronary artery HIPs by CKD grade

### CMR imaging

Non-contrast T1WI will be performed with a 3-T MR imager (MAGNETOM Verio; Siemens Healthineers, Erlangen, Germany) with a 32-channel (cardiac) coil at the National Cerebrovascular and Cardiovascular Center or Dokkyo Medical University Hospital, a 1.5-T MR imager (MAGNETOM Aera; Siemens Healthineers) with 18-channel (body) coils and 32-channel (spine) coils at the Ehime Prefectural Imabari Hospital, or a 1.5-T MR system (Achieva; Philips Healthcare, Best, the Netherlands) using a 32-element torso cardiac phased-array coil at the University of Tsukuba, Shin-Koga Hospital, Nihon University School of Medicine, or Kanagawa Cardiovascular and Respiratory Center. The procedures used to acquire CMR images at each institution are based on a standardized protocol (Supplementary Table 1).

### Core laboratory CMR analysis

All CMR images will be assessed by at least two trained observers who are unaware of patient data and used the T1W images to calculate PMR and CMRA images to evaluate vessel stenosis at the central core laboratory. The methods used to evaluate plaque images in this study have been described previously [6, 12]. In brief, in segment-based analysis, the highest signal intensity detected in each plaque will be considered the representative PMR value for that plaque. In patient-based analysis, the highest PMR among all coronary plaques is considered to be the PMR for that patient. Examination of coronary segments is limited to segments 1–3, 5–7, 9, and 11–13, based on recommendations from the American Heart Association [13].

The location of a coronary plaque is determined by careful comparison using fiduciary points on CMRA images. Once a coronary plaque has been confirmed with CMRA, the corresponding areas on T1W images were carefully matched using the surrounding cardiac and chest wall structures [6, 12, 14]. Regarding PMR quantification of coronary plaques that are not HIPs, when CMRA shows coronary stenosis in segments 1–3, 5–7, or 11–13, the PMR of the target lesion will be measured using the co-registration method described above.

### Definition of CAD

CAD is defined as a history of myocardial infarction, angina pectoris, PCI, CABG, or therapy with intracoronary fibrinolytic agents. In addition, patients will be classified based on CTCA or invasive coronary angiography showing the presence of the following for more than 1 year: (a) obstructive CAD if there is atherosclerotic plaque encompassing a luminal cross-sectional area of ≥ 70% in at least 1 major epicardial vessel or ≥ 50% in the left main trunk; (b) non-obstructive CAD if there is either atherosclerotic plaque encompassing a luminal cross-sectional area of < 70% but > 10% in at least 1 major epicardial vessel or a calcium score > 400 Hounsfield units; or (c) minimal or no CAD. Significant plaque burden is defined as atherosclerotic plaque causing > 10% luminal cross-sectional area stenosis.

### Data analysis

The trial results will be reported in accordance with CONSORT guidelines. When possible, the clinical profile of non-recruited and ineligible patients will be recorded. All imaging and laboratory data were analyzed by an independent attending physician and a radiologist at the National Cerebral and Cardiovascular Center or Tohoku University. These evaluators were blinded to patient treatment status. This study was approved by the institutional review boards (IRBs) of the National Cerebral and Cardiovascular Center (study no. R21022-3) and 7 other participating institutions (Supplementary Figure 1). Written informed consent will be obtained from all enrolled patients.

### Statistical analysis

The study statistician ([name]) will supervise statistical analyses performed by the Department of Preventive Medicine and Epidemiology, National Cerebral and Cardiovascular Center. A full statistical analysis plan will be prepared separately.

All analyses will perform according to the intention-to-treat principle. Missing data will be removed from the analyses, except for data on deaths, which are censored at the time the patient is lost from the trial. Endpoints will be analyzed with the use of Cox regression models, adjusted for center and minimization variables, and cumulative event curves will be constructed.

Data are reported as means and standard deviations, medians and interquartile ranges, and hazard ratios or odds ratios with 95% confidence intervals, as appropriate. All statistical analyses will be performed with SPSS software (version 24.0; IBM Corp, Armonk, NY), Stata 15 (StataCorp, College Station, TX), or R software (version 3.4.3; R Foundation for Statistical Computing). All *p* values < 0.05 will be considered statistically significant.

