### Study design

This is a multicenter, parallel-group, prospective randomized controlled, open-label, superiority trial to assess the impact of non-contrast T1WI and CMRA on the diagnosis and management of patients at high risk for CAD estimated based on CAD risk factor categories for a Japanese urban population (Suita score), which is composed of 8 coronary risk factor categories (Tables 1 and 2) [9, 10]. Eligible subjects are randomly assigned.

**Table 1 Tab1:** Suita score

Risk factor	Value	Score
Age (years)	35–44	30
	45–54	38
	55–64	45
	65–69	51
	> 70	53
Gender	Female	− 7
Current smoking	Yes	5
Diabetes mellitus	Yes	6
Blood pressure (mmHg)	Optimal (SBP < 120 and DBP < 80)	− 7
	Normal (SBP < 130, DBP < 85)	0
	High normal (SBP < 140 or DBP < 90)	0
	Stage I HTN (SBP 140–159 or DBP 90–99)	4
	Stage II–IV HTN (SBP 160–179 or DBP 100–109)	6
LDL-cholesterol (mg/dl)	< 100	0
	100–139	5
	140–159	7
	160–179	10
		11
HDL-cholesterol (mg/dl)	< 40	0
	40–59	− 5
	≥ 60	− 6
CKD	Stage I or II (eGFR > 60 ml/min/1.73 m^2^)	0
	Stage III (eGFR: 30–59 ml/min/1.73 m^2^)	3
	Stage 4 or 5 (eGFR < 30 ml/min/1.73 m^2^)	14

Weighted scoring of risk factors is used to categorize the 10-year risk of coronary heart disease. *CHD* coronary heart disease, *CKD* chronic kidney disease, *eGFR* estimated glomerular filtration rate, *DBP* diastolic blood pressure, *HDL* high-density lipoprotein, *HTN* hypertension, *LDL* low-density lipoprotein, *SBP* systolic blood pressure

**Table 2 Tab2:** Predicted probability of CHD in 10 years

Total Suita score	Estimated 10-year risk
< 35	< 1%
36–40	1%
41–45	2%
46–50	3%
51–55	5%
56–60	9%
61–65	14%
66–70	22%
> 71	> 28%

to the CMR group or the control group (allocation rate 1:1). The randomization stratified on the following variables: age, gender, presence or absence of type 2 diabetes mellitus, and CKD grade (Fig. 1).

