### Outcomes

#### Primary endpoint

The primary outcome is a composite of cardiovascular events at 1 year after study examinations: all-cause death, death from cardiovascular disease, nonfatal MI, nonfatal ischemic stroke, and ischemia-driven* unplanned coronary intervention (PCI or CABG).

*Myocardial ischemia diagnosed with stress myocardial single photon emission computing tomography (SPECT), or invasive fractional flow reserve.

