### Sample size

Based on the results of previous studies [6, 12, 14], we hypothesized that the 10-year probability of developing CAD would be ≥ 22% and that the effect of optimal drug therapy, such as a strong statin to reach the low-density lipoprotein (LDL) cholesterol control target and medications to reach the blood pressure control target, and the effect of screening with CMRA and non-contrast T1WI on patients with HIPs or coronary stenosis would result in 48–50% lower relative risk. The effect of early detection of coronary artery lesions (significant stenosis and unstable plaque) was estimated to result in a relative risk reduction of 48–50%. The SCOT-HEART study compared patients undergoing coronary CTCA versus conventional testing, similar to this study. The hazard ratio was 0.59 in the CTCA group compared with the conventional test group. We assumed that CTCA in the SCOT-HEART study [1, 15, 16] did not assess plaque instability and that CMR with analysis of HIPs could assess plaque instability better than CTCA alone. In a previous study [14], 77% of all cardiovascular events occurred within 2 years, and the event rate for HIP with signal intensity > 1.4 was approximately 30%; thus, an annual event rate of 11.6% was expected. Based on additional assumptions about an enrollment period of 3 years and a follow-up period of 3 years, power of 0.8, and two-sided *p* value of 0.05, a total of 524 patients would be needed with the dropout rate set at 5%.

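### The missing-data rule censors lost patients only for death, which gives no workable instruction for a composite of death and nonfatal events and sits against intention-to-treat

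*Protocol article*

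**What the plan says.** Three consecutive statements in the Statistical analysis section of the protocol article bear on this.

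- The principle: "All analyses will perform according to the intention-to-treat principle".
- The missing-data rule: "Missing data will be removed from the analyses, except for data on deaths, which are censored at the time the patient is lost".
- The model: "Endpoints will be analyzed with the use of Cox regression models, adjusted for center and minimization variables". Cumulative event curves are also promised.

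Under Primary endpoint, the outcome is a composite at 1 year of death, nonfatal MI, nonfatal ischemic stroke and unplanned ischemia-driven revascularisation. Under Secondary endpoints, the composite returns at 3 years. The Study design section describes a "multicenter, parallel-group, prospective randomized controlled, open-label, superiority trial". The Sample size section allows for 5% dropout in a total of 524 and does not split it by arm. The Statistical analysis section says that a full analysis plan will be prepared separately; it is not shown.

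**The concern.** Censoring at loss is offered only as an exception, for deaths. The natural reading is that nonfatal outcomes of a lost patient are removed instead. The analysed quantity, however, is one time to first event. Someone lost event-free at month 6 cannot contribute six months of follow-up to the death component and nothing to the MI, stroke and revascularisation components of the same variable. Two analysts could both claim to follow the sentence and analyse different sets of patients.

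If the choice falls on removal, retention depends on the outcome: an event before loss keeps the patient in, no event before loss takes the patient out. That departs from intention-to-treat. The trial is open-label and the arms undergo different tests, so unequal loss is possible, and unequal loss would then move the hazard ratio even with no true effect.

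**Working it through.** **Consistency of the rule.** For a patient lost event-free at time t:

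| Component | Instruction |
|---|---|
| Death | keep, censor at t |
| Nonfatal MI, stroke, revascularisation | remove |
| Composite time to first event | both at once |

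Nothing elsewhere in the article reconciles the last row.

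**Size if patients lost event-free are removed.** The article gives no figure for the effect of this rule, so there is none to reproduce.

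*Inputs from the Sample size section:* "an annual event rate of 11.6% was expected", so the hazard is λ = −ln(1 − 0.116) = 0.1233 per year; 5% dropout of 524 is about 26 patients.

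*Assumptions:* constant hazards, loss independent of event risk, and the split of loss by arm. A split of 8% control and 2% CMR over the follow-up averages the planned 5%: 0.08 × 262 + 0.02 × 262 ≈ 26.

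*Formulas,* with loss hazard γ and horizon τ:
- retained without an event: S = exp(−(λ+γ)τ)
- event before loss: E = λ/(λ+γ) × (1 − S)
- apparent risk after removal: p = E/(E + S)
- approximate hazard ratio: ln(1 − p_CMR) / ln(1 − p_control)

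*Equal loss, 5% per year (γ = 0.0513).*
- 1 year: S = 0.8398, E = 0.1131, p = 0.1131/0.9529 = 11.9%, against a true 11.6%.
- 3 years: S = 0.5923, E = 0.2879, p = 0.2879/0.8802 = 32.7%, against a true 30.9%.
- Both arms shift alike, so the hazard ratio does not move.

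*Unequal loss at 1 year, 8% control and 2% CMR, no true effect.*
- Control: γ = 0.0834, S = 0.8133, E = 0.1114, p = 0.1205, −ln(1 − p) = 0.1284.
- CMR: γ = 0.0202, S = 0.8663, E = 0.1149, p = 0.1171, −ln(1 − p) = 0.1245.
- Ratio: 0.1245/0.1284 = 0.97.

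*Same split, cumulative over 3 years.*
- Control: γ = 0.0834/3 = 0.0278, p = 0.3188, −ln(1 − p) = 0.3839.
- CMR: γ = 0.0202/3 = 0.0067, p = 0.3115, −ln(1 − p) = 0.3732.
- Ratio: 0.97.

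*8% versus 2% per year for 3 years.*
- Control: S = 0.5379, E = 0.2757, p = 0.3388, −ln(1 − p) = 0.4137.
- CMR: S = 0.6502, E = 0.3006, p = 0.3161, −ln(1 − p) = 0.3800.
- Ratio: 0.92.
- Total loss here is 1 − 0.92³ = 22% and 1 − 0.98³ = 6%, a mean of 14%, nearly three times the planned 5%.

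**Check by simulation with a Cox fit** (1,000,000 or more per arm):

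| Loss, control / CMR | True HR | Censor at loss | Remove if lost event-free |
|---|---|---|---|
| 5% / 5%, 1 year | 1.00 | 1.00 | 1.00 |
| 8% / 2%, 1 year | 1.00 | 1.00 | 0.97 |
| 2% / 8%, 1 year | 1.00 | 1.00 | 1.03 |
| 8% / 2%, 1 year | 0.50 | 0.50 | 0.49 |
| 8% / 2%, cumulative over 3 years | 1.00 | 1.00 | 0.97 |
| 8% / 2% per year, 3 years | 1.00 | 1.00 | 0.91–0.92 |

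The arm with more loss looks worse.

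**Against the trial's precision at 1 year.** Under the null, 262 × 0.116 ≈ 30 events per arm, so the standard error of the log hazard ratio is √(1/30.4 + 1/30.4) = 0.26. The shift |ln 0.97| = 0.030 is about 0.12 standard errors, which takes a two-sided 5% error rate to about 5.2%.

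**The case against.** The sentence speaks of missing data, not of patients. Cox regression and event curves normally handle loss by censoring, so removal may have been meant for endpoints such as prescription rates and goal attainment. The bias also needs one specific rule, which the text does not spell out: drop those lost event-free, keep those with an event before loss. If everyone ever lost were dropped, and loss were unrelated to risk, the hazard ratio would stay unbiased and only information would be lost. The separate analysis plan may settle the matter.

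Much of this stands. It makes the defect an unworkable, loosely worded rule and not a proven deletion. It does not rescue the sentence: the article itself fixes the rule and confines censoring to deaths, so this is more than a detail left to the analysis plan.

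A reader might also infer that randomised patients who withdraw are deleted, because the Exclusion criteria list a wish to discontinue or withdraw consent. That line is an entry in a pre-enrolment list. It looks misplaced, but says nothing about the analysis set after randomisation.

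**Conclusion.** The concern holds as a should-fix. The rule conflicts with the stated intention-to-treat principle and cannot be applied to a composite of death and nonfatal events; that is so at any rate of loss.

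The numerical consequence is modest. With loss at the planned level and an assumed 8% versus 2% split, the hazard ratio moves by about 3%, in either direction according to which arm loses more. A reader might infer a serious distortion from the 0.92 at 3 years, but that needs annual loss well above the planned dropout, with a split for which the article gives no figures.

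The sizes rest on constant hazards, loss independent of risk, the assumed splits, and the reading that only patients lost event-free are removed. Loss related to risk would bias plain censoring as well.

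**What to change.** Replace the missing-data sentence with: *All randomised patients enter the Cox models in their allocated arm; patients without an event are censored for the whole composite at the last date on which all components were ascertained; removal of missing values applies only to endpoints that are not time-to-event.*

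The cost is one sentence, carried unchanged into the analysis plan and settled before outcomes are compared by arm. Data collection and sample size are unaffected. Sensitivity analyses for informative loss are ordinary matter for the analysis plan and are not asked for here.

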### Sample size

Based on the results of previous studies [6, 12, 14], we hypothesized that the 10-year probability of developing CAD would be ≥ 22% and that the effect of optimal drug therapy, such as a strong statin to reach the low-density lipoprotein (LDL) cholesterol control target and medications to reach the blood pressure control target, and the effect of screening with CMRA and non-contrast T1WI on patients with HIPs or coronary stenosis would result in 48–50% lower relative risk. The effect of early detection of coronary artery lesions (significant stenosis and unstable plaque) was estimated to result in a relative risk reduction of 48–50%. The SCOT-HEART study compared patients undergoing coronary CTCA versus conventional testing, similar to this study. The hazard ratio was 0.59 in the CTCA group compared with the conventional test group. We assumed that CTCA in the SCOT-HEART study [1, 15, 16] did not assess plaque instability and that CMR with analysis of HIPs could assess plaque instability better than CTCA alone. In a previous study [14], 77% of all cardiovascular events occurred within 2 years, and the event rate for HIP with signal intensity > 1.4 was approximately 30%; thus, an annual event rate of 11.6% was expected. Based on additional assumptions about an enrollment period of 3 years and a follow-up period of 3 years, power of 0.8, and two-sided *p* value of 0.05, a total of 524 patients would be needed with the dropout rate set at 5%.

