### Inclusion and exclusion criteria

#### Inclusion criteria

Study participants must meet all of the following criteria:Age of 20–85 yearsDiagnosis of hypertension, type 2 diabetes mellitus, non-cardiogenic cerebral infarction, peripheral arterial disease, carotid stenosis, aortic disease, or dyslipidemiaGrade ≥ 3 CKD with estimated glomerular filtration rate (eGFR) < 60 ml/min/1.73 m^2^ and very high risk for CAD, with a Suita score of ≥66 points with a predicted 10-year incidence of a coronary event of >22%Capable of visiting a study center on an outpatient basisCapable of providing written informed consent before study participation

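### The 11.6% annual event rate behind the sample size is that of HIP-positive patients in an earlier study, not of the population this trial randomises, so the stated 80% power is unsupported

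*Protocol article*

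**What the plan says.** All the planning inputs stand in the Sample size section of the protocol article.

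- **Event rate.** Two facts are taken from an earlier study. One is that "77% of all cardiovascular events occurred within 2 years". The other leads straight to the planning rate: "the event rate for HIP with signal intensity > 1.4 was approximately 30%; thus, an annual event rate of 11.6% was expected".
- **Population risk.** The same paragraph opens with another figure: "we hypothesized that the 10-year probability of developing CAD would be ≥ 22" per cent.
- **Effect.** Screening and drug therapy "on patients with HIPs or coronary stenosis would result in 48–50% lower relative risk". The paragraph also cites a hazard ratio of 0.59 from a trial of CT coronary angiography against conventional testing.
- **Result.** 524 patients in total, for power 0.8 at two-sided 0.05, 3 years of enrolment, 3 years of follow-up and 5% dropout.

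The Inclusion criteria select on CKD grade 3 or worse and "Suita score of ≥66 points with a predicted 10-year incidence of a coronary event of >22" per cent. No plaque finding is required. Under Interventions, only the CMR group has T1-weighted imaging. Under Primary endpoint, the outcome is a 1-year composite that includes all-cause death and nonfatal ischemic stroke.

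**The concern.** A control-arm rate used for sizing should describe the patients who will be randomised. The 11.6% describes those who already had a high-intensity plaque above 1.4 in another cohort. The trial will enrol patients with and without such plaques. The paragraph gives no expected share of HIP-positive patients and no step that dilutes the rate for the others.

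If the enrolled population has a lower rate, the trial collects fewer events than planned and has less than 80% power. A non-significant result could then not be read as evidence against CMR screening. The type I error and the estimate itself are not affected.

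**Working it through.** **1. Where 11.6% comes from.** 30% events in the HIP > 1.4 group, 77% of events within 2 years: 0.30 × 0.77 / 2 = 0.1155, or about 11.6% a year.

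**2. The plan's own figure.** The article does not name its formula. Among the standard variants tried, one returns 524:

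- Freedman events at hazard ratio (HR) 0.59: (1.960 + 0.842)² × (1.59 / 0.41)² = 118.04, rounded up to 119.
- Control risk at hazard 0.116 over 3 years: 1 − exp(−0.348) = 0.294. CMR risk at 0.116 × 0.59: 0.186. Mean 0.240.
- 119 / 0.240 gives 497 evaluable patients, and 497 / 0.95 gives 524.

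The full 11.6% is used here for the whole control arm. The match was found by search, so it corroborates the reading but does not prove the sponsor's method. The same calculation with HR 0.50–0.52 gives only 331–363 patients.

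**3. The population risk the documents state.** −ln(1 − 0.22) / 10 = 0.0248 a year, more than four times below 0.116. Table 2 gives above 28% for the top score band: −ln(1 − 0.28) / 10 = 0.0329 a year.

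**4. Power of the planned trial.** Evaluable patients: 524 × 0.95 ≈ 498, or 249 per arm. Expected events: D = 249 × [(1 − exp(−λT)) + (1 − exp(−λ·HR·T))]. Schoenfeld power: Φ(½·√D·|ln HR| − 1.96). Example: λ = 0.0248, T = 3, HR 0.59 gives D = 28.5 and power Φ(1.408 − 1.960) = 0.29.

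| Control hazard per year | 3 years: HR 0.59 / 0.52 / 0.50 | 1 year: HR 0.59 / 0.52 / 0.50 |
|---|---|---|
| 2.5% (22% in 10 years) | 0.29 / 0.40 / 0.44 | 0.13 / 0.17 / 0.18 |
| 5% (assumed) | 0.50 / 0.67 / 0.71 | 0.21 / 0.29 / 0.32 |
| 8% (assumed) | 0.69 / 0.84 / 0.88 | 0.31 / 0.42 / 0.46 |
| 11.6% (as stated) | 0.82 / 0.94 / 0.96 | 0.42 / 0.56 / 0.61 |

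The 2.5% row means about 27–29 events at 3 years and 9–10 at 1 year.

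**5. Rate needed for 80% power at 3 years.** Solving the same formula for λ gives 10.9% a year at HR 0.59, 7.1% at HR 0.52 and 6.3% at HR 0.50.

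**6. Illustration of dilution only.** The inputs here are not in the documents. Suppose 30% are HIP-positive at 11.6% a year with risk halved by CMR, and the rest run at 1.0% a year, unaffected. The overall control rate is 0.3 × 0.116 + 0.7 × 0.010 = 0.0418. The CMR rate is 0.3 × 0.058 + 0.7 × 0.010 = 0.0244. The ratio is 0.58, not 0.50. With the rest at 2.2% the rates are 0.0502 and 0.0328, ratio 0.65. Dilution thus lowers the rate and weakens the effect together.

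**The case against.** The strongest reply is that 2.5% a year is not the primary-endpoint rate. This stands. The 22% is a lower bound and covers coronary disease only. The composite adds all-cause death and ischemic stroke in CKD patients aged up to 85, some with cerebral infarction or peripheral arterial disease. A reader might infer that the trial has nowhere near its stated power, but the documents give no composite rate and so cannot show that. At 8% a year with HR 0.50–0.52, 3-year power is 0.84–0.88.

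A reader might also infer that the 48–50% reduction in plaque-positive patients was the effect used to size the whole trial. The arithmetic does not support this: 524 is reproduced with 0.59, which the article presents as a comparison of whole arms. The wording is also not clear on whether the 48–50% is confined to patients with HIP or stenosis.

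Nor can it be said that 11.6% carried over 3 years exceeds the source group's total of 30%. Read as a hazard, it gives 29.4%.

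Finally, the low 1-year power is partly a separate matter. Even at the full 11.6% it is 0.42–0.61, and that loss comes from sizing on 3 years for a 1-year endpoint.

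None of this supplies a reason for using the HIP > 1.4 rate. The rate was not derived by adding deaths and strokes to the coronary risk. Nor is this an omission explained by a condensed article: the article states its derivation, and that derivation does not match its eligibility criteria.

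**Conclusion.** The point holds: the 11.6% belongs to a marker-positive subgroup of an earlier study and is used without adjustment for a population not selected on that marker. The stated 80% power for 524 patients is therefore unsupported.

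The size of the loss depends on a composite rate that the documents do not give. From 2.5% (a floor) to 8% a year (assumed), 3-year power runs from 0.29 to 0.88 over HR 0.59 to 0.50. At HR 0.59, the value that reproduces 524, the enrolled population would need nearly the subgroup's rate (about 11% a year) for 80%. At HR 0.50–0.52 about 6.3–7.1% would do. At the 1-year primary endpoint, no rate up to 11.6% gives 80% under any of these hazard ratios. These figures assume constant hazards, 498 evaluable patients and an effect that applies to the whole arm.

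**What to change.** Rewrite the Sample size section in three steps.

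1. Replace 11.6% with a justified control-arm rate of the full composite for all eligible patients. One way is to weight it: share with HIP or stenosis × their rate, plus share without × theirs, with sources for each input.
2. State the single whole-arm hazard ratio used, 0.59 or 0.50–0.52. If the reduction is meant only for patients with HIP or stenosis, dilute it by their share.
3. Restate the power of 524 patients at 1 year and at 3 years over a stated range of rates.

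The table should inform readers about power; it should not be used as grounds for changing the primary horizon of a trial that is already recruiting. The cost is a rewritten paragraph and a less favourable stated power. No extra patients are needed for this correction.

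### The sample size of 524 with 80% power does not follow from the stated inputs on any follow-up the protocol describes; those inputs need about 192–388 patients, depending on the reading

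*Protocol article*

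**What the plan says.** The Sample size section of the protocol article gives these inputs.

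- Event rate: "an annual event rate of 11.6% was expected".
- Effect: early detection of lesions "was estimated to result in a relative risk reduction of 48–50" per cent. The same range appears earlier in the section for treatment and screening combined ("would result in 48–50% lower relative risk").
- Time: "an enrollment period of 3 years and a follow-up period of 3 years".
- Error rates: power 0.8 and a "two-sided *p* value of 0.05".
- Result: "a total of 524 patients would be needed with the dropout rate set at 5" per cent.

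The section also cites an earlier CT angiography trial: "The hazard ratio was 0.59 in the CTCA group compared with the conventional test group". It presents this as support, arguing that CMR should do better, and not as the design effect.

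Elsewhere in the article, allocation is 1:1 with 262 per arm (Patient eligibility and recruitment) and endpoints are analysed by Cox regression (Statistical analysis). Outcomes are assessed over 1 and 3 years (Patient eligibility and recruitment). Follow-up runs to 144 weeks after allocation (Study procedures). The primary outcome is a composite at 1 year (Primary endpoint).

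**The concern.** The paragraph supplies every quantity that a standard time-to-event calculation needs, so a reader can rerun it. An 11.6% annual rate, a halving of risk and about 3 years of observation per patient should need far fewer than 524 patients for 80% power.

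This paragraph is the article's only justification of N and its only statement of what the trial can detect. If its parts do not belong together, neither a null nor a positive result can be read against the design. A reader cannot tell whether the trial has 80% power for the claimed effect, nearly certain power, or less than 80%.

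**Working it through.** **Control rate.** The article's figure reproduces: 0.30 × 0.77 / 2 = 11.55% per year, or 11.6%. As a hazard this is 0.116 if used directly, or −ln(1 − 0.116) = 0.1233 if 11.6% is an annual risk. Both were tried.

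**Effect.** A 48–50% reduction was read in two ways.
- As a hazard ratio (HR): 0.50–0.52.
- As a ratio of annual risks: 11.6% versus 5.8% gives HR = ln(0.942)/ln(0.884) = 0.485; 11.6% versus 6.03% gives 0.505.

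**Events for 80% power, two-sided 0.05.**
- Schoenfeld, d = 4(1.960 + 0.842)²/(ln HR)²: 65.3 at HR 0.50 and 73.4 at HR 0.52; 59.8 and 67.1 on the annual-risk scale.
- Freedman, d = (1.960 + 0.842)²[(1 + HR)/(1 − HR)]²: 70.6 and 78.7; 65.1 and 72.4 on the annual-risk scale.

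**Event probability** (exponential times).
- Fixed time T per patient: 1 − exp(−λT).
- Uniform accrual over A years plus F further years: 1 − [exp(−λF) − exp(−λ(A + F))]/(λA).

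N = d / (mean probability of the two arms) / 0.95.

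**Total N with 5% dropout, for the stated 48–50% effect:**

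| Time structure | HR, Schoenfeld | HR, Freedman | Annual risks, Schoenfeld | Annual risks, Freedman |
|---|---|---|---|---|
| 3 y accrual + 3 y further | 207–241 | 224–259 | 192–212 | 209–229 |
| 3 y per patient | 288–336 | 311–361 | 266–295 | 290–318 |
| 144 weeks per patient | 309–362 | 334–388 | 286–317 | 311–342 |

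Worked example: 3 years per patient, HR 0.50, hazard 0.1233. Mean probability = (0.3092 + 0.1689)/2 = 0.2390; 65.3/0.2390 = 273; 273/0.95 = 288.

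No cell reaches 400.

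**Power of 524.** Evaluable patients: 524 × 0.95 = 498. Power = Φ(√(498 × mean probability)/2 × |ln HR| − 1.960).
- Lowest case (144 weeks, HR 0.52, hazard 0.116, mean probability 0.2136): 106.4 events, power 0.92.
- Highest case (3 + 3 years, annual risks 11.6% versus 5.8%, mean probability 0.3286): 163.6 events, power 0.996.

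**What does come near 524.**
- Whole study closes 3 years after the first patient (A = 3, F = 0), Schoenfeld: 507–561 with the effect as annual risks, 548–642 with it as HR 0.50–0.52. The annual-risk range brackets 524 inside the stated effect.
- A 0.59 effect with 3 years or 144 weeks per patient: 431–557 over both formulas and both scales.

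**1-year primary endpoint.** Same formula with T = 1 and 498 evaluable.
- HR 0.52, hazard 0.116: mean probability 0.0840, 41.8 events, power 0.56.
- Annual risks 11.6% versus 5.8%: mean probability 0.0870, 43.3 events, power 0.66.

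**The case against.** The strongest reply is that 524 is recoverable. The article speaks of relative risk and an annual rate. Read on that scale, with accrual and follow-up together lasting 3 years, the written effect, rate, error levels and dropout give 507–561. Only the time structure would then be misdescribed, and about 80% power would be roughly right for that structure (77–81% by Schoenfeld). This stands as a plausible account of how the number arose. It does not rescue the paragraph. Mean follow-up would be about 1.5 years, against the 3 years written there and the 144 weeks in Study procedures, and late enrollees would not reach even the 1-year endpoint.

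A second reply is that the article condenses a fuller protocol and ties the 48–50% to patients with high-intensity plaque or stenosis, so a diluted effect such as 0.59 may have been entered for the whole arm. That is possible. But then the effect printed beside 524 is not the one that produced it.

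Three stronger readings are tempting and not supported.

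- A reader might infer that the inputs give roughly 208–242 and that N is more than twice what is needed. That is only the Schoenfeld answer for 3 + 3 years with the effect as a hazard ratio. The per-patient follow-up described elsewhere gives 266–388.
- A reader might infer that 0.48 was entered by mistake for a 48% reduction, since HR 0.48 with hazard 0.116 and closure at 3 years gives 523. Other routes reach the same neighbourhood within the stated effect, so this is conjecture.
- A reader might infer that the trial is simply overpowered and N is safe. At the 1-year primary endpoint the mismatch runs the other way.

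**Conclusion.** The point holds. On the follow-up the article describes, its inputs require about 192–259 patients (3 + 3 years) or 266–388 (3 years or 144 weeks each), so 524 is about 1.35 (524/388) to 2.7 (524/192) times the need. Power for the written effect would be about 92% to over 99%, not 80%. Which inputs were actually run is unknown; every route found to a figure near 524 contradicts either the stated follow-up or the stated effect.

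The result assumes exponential event times, uniform accrual, 1:1 allocation and 5% dropout taken as a loss of evaluable patients. It does not depend on the choice between Schoenfeld and Freedman, between the two hazards, or between the two effect scales. The 56–66% at 1 year further assumes that the 11.6% rate and the 48–50% effect both apply in the first year.

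**What to change.** Rerun the calculation and restate the Sample size paragraph so that these items agree with each other and with Patient eligibility and recruitment and Study procedures:

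- one effect value in place of a range, with its scale (hazard ratio or ratio of annual risks);
- the control rate;
- the accrual time and the follow-up per patient;
- N and power.

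If 524 came from a study closing at 3 years, or from a different effect, the follow-up or effect sentence should say so.

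In the same paragraph, state the power that 524 gives for the 1-year primary endpoint, about 56–66% for the written effect and rate. Replacing 0.8 by the 92–99% that the longer follow-up yields, without saying that it does not apply to the 1-year primary analysis, would exchange one misstatement for another.

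The cost is a short recalculation and a corrected paragraph, and a stated power that may be less favourable than 80%. Whether 524 should stand can be judged only once the paragraph and the primary endpoint refer to the same horizon.
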